#### 4.4.4 Treatment Structure

The intensive lifestyle intervention includes three phases: a lifestyle change (LC) phase of weekly sessions for months 1-6, followed by a bi-weekly lifestyle maintenance (LM) phase through months 7-12, and a continued contact (CC) phase from months 13 through the end of the study. The CC phase sessions are scheduled monthly for the initial 12 months (study months 13-24) and then quarterly or 4 times a year to the end of the study. During the LM and CC phases, telephone calls are held between visits. Limited intensification may occur in LM and CC phases when needed due to failure to make or maintain progress toward target goals.

The TLP is primarily an individual-based rather than group-based model of treatment because of the range of developmental stages of the participants as well as the anticipated geographic distances between participants and the clinics. Opportunities for group interactions, such as group walks and special events, may be scheduled over the entire duration of the trial to provide opportunities to incorporate the benefits of group involvement.

The format and structure of weekly family sessions remains the same during all phases of the lifestyle intervention. Each session includes reviewing short- and long-term goals, developing strategies to achieve these goals, praising successes, and problem solving in areas of difficulty. Each session includes a combination of separate and concurrent sessions by the youth and the parents. This format allows individual time for the therapist to address important developmental issues with the adolescent and provide appropriate parenting strategies/interventions for the parent. During "off periods" when not in session with the therapist, the participant completes behavior change related educational activities.

Sessions are audiotaped and some tapes are reviewed by the PAL's Ph.D. level behaviorist and the Lifestyle Resource Core.

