#### 4.7 Add-on Insulin Therapy

- *Failure to maintain adequate metabolic control:* If HbA1c  $\geq$  8.0%, therapy is re-invigorated by more frequent telephone contact and visits. If HbA1c remains  $\geq$  8% throughout the next six months, then the patient is classified as failing to maintain

adequate metabolic control and *if* the participant's fasting blood glucose values are not in target then add-on therapy with insulin is initiated.

- *Outcome assessments before the initiation of add-on insulin therapy:* Before starting insulin treatment, participants undergo a comprehensive outcomes assessment unless this has been completed within the past three months.
- *Add-on insulin treatment regimen:* Patients who meet criteria for add-on insulin therapy continue to take the study drug metformin but discontinue the study drug rosiglitazone. The patients and clinicians remain masked to the treatment assignment but are unmasked to HbA1c. Initial insulin treatment is glargine insulin, 0.2 units per kilogram given in the evening. The dose is increased up to 1.0 U/kg/day (to a maximum of 100 units), until fasting blood glucose (FBG) values between 70-150 mg/dL are achieved.  
Add-on glargine insulin therapy is considered unsuccessful if (1) 1.0 U/kg/day (to a maximum of 100 units) does not bring FBG to target within 1 month or (2) HbA1c > 8% at 3 months or (3) HbA1c > 7% at 6 months. At that point, insulin therapy—including adding rapid, short, or intermediate acting insulin—is provided at the clinician's discretion.
- *Self-monitoring of blood glucose (SMBG):* During insulin therapy, patients are asked to monitor blood glucose levels at least four times a day. Target fasting glucose and pre-meal glucose is 70-150 mg/dL and the target peak postprandial glucose is  $\leq 200$  mg/dL.

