- Urine ketones are measured as indicated if BG > 300 mg/dL.
- Serum creatinine is used to calculate creatinine clearance.
- If transaminases > 1.5 ULN, safety protocol is followed.
- Other anthropometric measurements are waist circumference and abdominal height.
- Screening lipid values are LDL and TG for determining eligibility. Other lipid assays include free fatty acids, lipoprotein subclass levels, average LDL particle density, and total ApoB levels.
- A comprehensive physical exam including Tanner stage and evaluation of acanthosis nigricans is performed at screening, baseline, all annual visits, and outcome. Otherwise a targeted physical exam is performed (every 2 months in year 1 follow-up and then quarterly).
- The FFQ is used for nutrition, 3-day PDPAR and 7-day recorded accelerometer for physical activity, and PWC 170 for fitness.
- The psychosocial and quality of life battery includes CDI, BDI, EDEQ (and QEWP-R if participant has high score on the EDEQ), PEDS QL, and HUI-2.
- Cardiovascular risk factors include measurement of fibrinogen, c-reactive protein, homocysteine (vitamin B-12 will be obtained to assess homocysteine), plasminogen activator inhibitor-1, interleukin-6. Pro-inflammatory and hemostasis markers are assayed at baseline, 6 months, 12 months, and end of study; blood from other draws is stored.
- Participants are asked about adverse events (AE) at clinic visits, but AE and SAE (serious adverse events) may be reported by the patient at any time.
- Data collected from the biological parent at baseline are height, weight, BDI, and EDEQ (and QEWP-R depending on EDEQ high score).
- Survey data include BDI, EDEQ (and QEWP-R depending on EDEQ high score), PEDS QL (adult proxy) and CHQ (P28).
- Data are collected every 2 months during the first year and quarterly thereafter from clinic staff on time spent for patient treatment. Logbook data are collected from clinic

staff every four months to further assess time spent providing treatment. Data are collected from patients and families regarding time and resource use related to treatment at baseline, 6 months, annually, primary endpoint, and at study closeout.

(p) The last HbA1c value during run-in is considered the baseline HbA1c.

(q) A sample of blood for DNA may be collected any one time after randomization.

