#### 6.2.2 Laboratory Monitoring

The purpose of periodic laboratory monitoring is to identify changes in health status that increase the risks associated with study medication (metformin and/or TZD), and to identify changes in health status as a result of participation in the trial.

After randomization, all study participants have blood glucose, SGPT/ALT, and SGOT/AST determined at every visit (every two months for the first year followed by every three months thereafter). Calculated creatinine clearance is determined at baseline and

annually. Urine ketones are measured if BG > 300 mg/dL at any clinic visit. Hemoglobin and hematocrit are measured at baseline, 2 and 6 months, and annually.

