#### 6.4.2 Definitions of Adverse Events

- *Adverse Event (AE)*: Any unfavorable and unintended change in the structure, function or chemistry of the body experienced by a study participant during the study regardless of the relationship of this change to administration of study intervention or participation in the study. Adverse events include symptoms and changes in laboratory data that are not specifically part of the primary or secondary outcomes of the trial. AEs are reported only at scheduled study visits unless they meet the criteria for being serious.
- *Serious Adverse Event (SAE)*: Events are divided into those that are serious (SAEs) and those that are not serious (AEs). The distinction between an SAE and an AE is a regulatory definition established by the FDA, not a clinical definition. The definition of SAE is not always related to clinical severity of the event. An AE is considered serious (SAE) when it satisfies any one of the following criteria:
  - a. The event results in an inpatient hospitalization (any overnight stay associated with an admission).
  - b. The event results in the prolongation of a hospital stay.
  - c. The event results in permanent or severe disability.
  - d. The event results in death.
  - e. A pregnancy results in a congenital anomaly.
  - f. The event results from an overdose (either accidental or experimental) of the study medication.
  - g. The event is life-threatening.
  - h. Treatment is required to prevent a serious event.
  - i. The patient experiences a bout of lactic acidosis.
  - j. An episode of severe hypoglycemia occurs.

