#### 6.4.3 Non-serious Adverse Events

It is essential that AEs be ascertained in an unbiased manner using standard questions that are identical and identically administered to patients in all three treatment arms. Therefore, AEs are reported on a standard form that is completed by the study staff at each regular follow-up visit. AEs are ascertained by asking targeted questions relating to specific events of import in diabetic patients on any of the study treatment arms. AEs also include any significantly abnormal physical finding identified on examination and any significantly abnormal laboratory result obtained on the patient between visits or at the time of the visit. Questions answered YES and any new abnormal physical findings are pursued by the study staff in order to determine the seriousness of the event and the need for further evaluation, follow-up, or referral. Adverse events reported or ascertained between clinic visits are captured and reported at the time of the next scheduled visit.

Pre-existing conditions (that is, conditions present prior to randomization) are not considered or recorded as AEs or SAEs unless the condition worsens in intensity or frequency after randomization. Likewise, continuing adverse events are not reported as AEs at subsequent visits unless they increase in severity or frequency between the visits, they result in criteria for an SAE, and/or they resolve between visits.

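### Non-serious AEs volunteered between visits join the elicited ones with no source marked, although opportunity to volunteer them differs by arm

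*Protocol*

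**What the plan says.** Section 6.4.3 sets the standard: AEs are to be "ascertained in an unbiased manner using standard questions that are identical and identically administered to patients in all three treatment arms". To that end, study staff complete a standard form with targeted questions at each regular follow-up visit. The same paragraph ends: "Adverse events reported or ascertained between clinic visits are captured and reported at the time of the next scheduled visit".

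Two other places bear on the between-visit stream. A note to the data collection table in section 5.1 states that "AE and SAE (serious adverse events) may be reported by the patient at any time". Section 6.4.2 states that "AEs are reported only at scheduled study visits unless they meet the criteria for being serious". Read with 6.4.3, this fixes when a non-serious event is entered, not where it came from.

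On contact, section 6.2.2 gives the medical visits common to all arms: "every two months for the first year followed by every three months thereafter". Section 4.4.4 gives the lifestyle arm alone "a lifestyle change (LC) phase of weekly sessions for months 1-6", then bi-weekly sessions in months 7-12, monthly sessions in months 13-24 and quarterly sessions after that, with telephone calls between visits in the later phases. Under section 4.7, when HbA1c is at or above 8%, "therapy is re-invigorated by more frequent telephone contact and visits"; this applies in any arm.

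Section 2.2.2 compares the number of patients with treatment-related side effects among the three arms.

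**The concern.** The elicited stream is the same in every arm: same form, same questions, same visits. The between-visit stream depends on how often a patient speaks to staff, and that differs by arm. Once the two are merged without a source marker, the record no longer meets the standard that the section sets for itself, and nobody can separate the streams afterwards.

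The events at risk are mild and easily forgotten by the next visit. Gastrointestinal complaints are named in section 2.2.2. Muscle soreness and activity injuries are named in section 6.2.3 as risks of the lifestyle program. If these are captured more completely in one arm, an apparent excess there may reflect recording only, and a true excess in a drug arm may be diluted. Safety comparison is the first secondary aim listed in section 1.1.

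**Working it through.** **Step 1. Scheduled contacts.** The protocol states no total, so there is no figure to reproduce. The inputs are the visit schedule (section 6.2.2), the session schedule (section 4.4.4) and the two-year minimum follow-up (section 1.2).

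- Medical visits, every arm: 6 in year 1, then 4 per year.
- Lifestyle sessions: 26 weekly + 13 bi-weekly = 39 in year 1; 12 in year 2; then 4 per year.
- Ratio = (medical visits + lifestyle sessions) / medical visits.

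| Period | Medical visits | Lifestyle sessions | Contacts, lifestyle v other | Ratio |
|---|---|---|---|---|
| Year 1 | 6 | 39 | 45 v 6 | 7.5 |
| Year 2 | 4 | 12 | 16 v 4 | 4.0 |
| First two years | 10 | 51 | 61 v 10 | 6.1 |
| Each year from year 3 | 4 | 4 | 8 v 4 | 2.0 |
| First five years | 22 | 63 | 85 v 22 | 3.9 |

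If every medical visit coincides with a session, the two-year ratio is 51/10 = 5.1. The number of telephone calls is not stated. Assuming one per gap between sessions (13 in months 7-12 and 12 in year 2), it is (61 + 25)/10 = 8.6. The extra contacts under section 4.7 are not quantified and cannot be added.

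**Step 2. What these contacts mean for AE capture.** They are occasions on which an event could be mentioned, not occasions on which anyone asks. Turning one into the other needs probabilities that the protocol does not give. Two illustrations, both on assumed inputs and with equal true rates in the arms, show how far the answer depends on them.

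*Events, year 1.* Let e be the chance that an event is elicited at the next visit, v the chance that it is volunteered at each extra contact, and k = 3.25 the mean number of extra contacts before the next visit. (An event falls on average halfway between visits: 26/3/2 = 4.33 sessions in months 1-6 and 13/3/2 = 2.17 in months 7-12; the mean is 3.25.)

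Recorded ratio = [1 - (1 - e)(1 - v)^k] / e.

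With e from 0.5 to 0.9 and v from 0.02 to 0.10, the ratio runs from 1.007 (e = 0.9, v = 0.02) to 1.29 (e = 0.5, v = 0.10).

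*Patients with at least one recorded event.* Assume 60-80% of events are recalled at the visit and extra contacts recover 25-50% of the rest.

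- One event per affected patient: the ratio runs from (0.80 + 0.20 × 0.25)/0.80 = 1.06 to (0.60 + 0.40 × 0.50)/0.60 = 1.33. With 250 per arm and 30-70% of patients affected, a two-sided two-proportion z-test gives nominal p < 0.05 with chance 7% to 89%.
- The 1.33 case with two events per affected patient: (1 - 0.2²)/(1 - 0.4²) = 0.96/0.84 = 1.14.
- The 1.33 case with three events: (1 - 0.2³)/(1 - 0.4³) = 0.992/0.936 = 1.06. At 70% affected, the chance of p < 0.05 falls from 89% to about 15%.

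The patient count in section 2.2.2 is thus less sensitive when affected patients have repeated events.

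**Step 3. Which outcomes are exposed.** Transaminases, hemoglobin and creatinine follow one schedule in all arms (section 6.2.2). Weight is measured at every visit (section 5.1). Clinically significant edema is an examination finding (section 6.2.4), and examinations are on the common schedule. Severe hypoglycemia is an SAE (section 6.4.2). That leaves symptom-based, non-serious events.

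**The case against.** The strongest reply is that nothing makes lifestyle sessions a route for AE reporting. Section 4.4.4 describes their content as goals, strategies, praise and problem solving, with no AE inquiry. The standard form is completed at the common visits, and any patient in any arm may report at any time. This stands as a limit: 61 v 10 is a ratio of contacts, not of AE ascertainments. It does not remove the point. Section 9.3 treats the lifestyle interventionist as study staff, and a stomach upset or injury mentioned at a weekly session fits the wording of 6.4.3 on between-visit reports.

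A reader might infer a definite tilt against the lifestyle arm of about sixfold, or a known false-positive rate. The documents support neither. The ratio of about six holds only for the first two years. The extra contacts in section 4.7 go to whichever arm has worse control, so they could offset the lifestyle excess if that is a drug-only arm. The 7% to 89% range rests wholly on assumed inputs and on one event per patient.

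A reader might also infer that edema, laboratory findings or severe hypoglycemia are distorted; step 3 shows that they are largely not. Gastrointestinal complaints are the main exposed item named in section 2.2.2, and section 6.2.4 expects few additional ones after run-in.

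Finally, which events enter a table is normally settled in the SAP, and form details in the manual of procedures. That is fair for the choice of table. Source is different: if it is not captured when the event is recorded, a later analysis plan cannot reliably recover it.

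**Conclusion.** The point holds in limited form. Section 6.4.3 sets a standard of identical ascertainment and, in the same paragraph, admits a stream that does not meet it, with nothing in the protocol to tell the two apart. Unequal opportunity follows directly from the schedule: 61 v 10 scheduled contacts over two years, 2 to 1 in each year from year 3, plus unquantified extra contacts for patients with HbA1c at or above 8% in any arm.

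Mild symptom-based AEs are probably inflated in the lifestyle arm, on the assumption that some patients mention events to lifestyle staff that they would not recall at the next visit. How large the effect is cannot be derived from the protocol; the illustrations run from about 1% to about 33% inflation on assumed inputs. The net direction is likely but not certain. Metformin alone against metformin plus rosiglitazone is touched only through section 4.7.

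**What to change.** 1. Add a source field to the AE form with two values: elicited by the standard questions, examination or laboratory tests at a scheduled medical visit; or known only from a between-visit report, a lifestyle session or an extra contact.
2. Add a rule for overlap: an event answered YES to the standard question at the next scheduled visit counts as elicited, even if it was mentioned earlier. Without this rule the field is ambiguous.
3. State in sections 6.4.3 and 2.2.2 that the between-arm comparison of non-serious symptom AEs uses elicited events, with the all-events table shown beside it.
4. Keep sending all events to the DSMB, and leave SAE reporting unchanged.

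The cost is one form field, the overlap rule and a sentence in each of the two sections. Some true between-visit events will count only in the second table, but no safety information is lost. If the form or the manual of procedures already records source, only the overlap rule and the statements in the protocol are needed.

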#### 6.4.4 Serious Adverse Events

Study patients are instructed to contact the clinic with any serious adverse event meeting the above criteria. Each SAE is recorded on the study form and sent to the CoC as soon as possible after they occur and preferably within 24 hours of the notification of the clinic staff. This notification should occur even if data are incomplete. Additional data and follow-up information are sent subsequently as an update to the original report. The CoC immediately forwards SAE reports to the study chair, the NIDDK project office, chair of the Safety and Monitoring Committee, and the DSMB, which convenes expeditiously at the discretion of the chair.

SAEs are also reported to the local IRB and any other institutional monitoring committee, as per local requirements. SAEs are also reported to the FDA if the study is operating under an IND.

#### 6.4.5 Tracking of Adverse Events by the Study Group

- *Serious adverse events:* All SAEs are reported to the CoC within 24 hours. The CoC forwards all SAE reports to the chair of the Safety and Monitoring Committee for consideration. The committee chair assesses each event to determine if immediate action is required by the study group in response to the event. If the chair determines that immediate action should be considered, he/she consults with other members of the committee to recommend a course of action. In addition, any SAE that results in death or permanent or severe disability and any SAE judged by the local PI as PROBABLY or DEFINITELY related to study participation are discussed by the committee as soon as feasible. Any actions recommended are communicated to the study chair for consideration of study wide action. If the SAE is not deemed to warrant immediate study wide action, it is discussed at the next scheduled meeting of the Safety and Monitoring Committee.
- *Non-serious adverse events:* Non-serious adverse events (AEs) are tabulated by the Coordinating Center in the same format as is done for the Data and Safety Monitoring Board (DSMB). Summaries of the AEs, tabulated by clinic, are provided to the Safety and Monitoring Committee and discussed by them before each Steering Committee meeting. The committee reviews this summary during one of its regularly scheduled meetings and makes recommendations for action to the study group at the next Steering Committee meeting.
- *Meetings of the Safety and Monitoring Committee (SMC):* The SMC meets in person at the time of each study group meeting and by conference call at least every 4-6 weeks. During these meetings, the committee discusses all SAEs and, when available, the summary reports of the non-serious AEs. The committee considers whether changes in the protocol (monitoring, consent process, etc.) are indicated based on the occurrence, frequency, or severity of AEs and SAEs. The committee also evaluates whether there is any clustering of AEs by clinic. As deemed necessary, a member of the SMC

communicates with the local center PI to obtain additional information about SAEs and observed local trends in non-serious AEs. The SMC remains blinded to patient treatment group. If an SAE or pattern of AEs warrants unblinding, the issue is referred to the DSMB.

## 7 Data Processing and Management

The CoC develops and maintains a central database integrating all of the project data.

### 7.1 Data Management System

Data are entered at the clinical centers into a web data entry application that facilitates direct entry of study data into the study's database. The web application guides the study staff member through the data entry process. If an invalid response is entered, the website signals and provides a message about the error and how to solve it. At any point during entry, the staff member can make an electronic note concerning a particular response. Valid individual responses are saved as soon as they are entered. The system includes programmed skip patterns as required by the case report forms, and also includes quality control checks such as lists of valid values for multiple choice items. The system provides automated consistency checking so the study staff can resolve inconsistencies quickly without a lengthy communication with the coordinating center. The same checking is also run on the central database at the coordinating center to verify that centers are resolving consistency checks.

The CoC provides a number of reports that help the study staff manage the study at their clinic, for example, graphs of recruitment versus goal by race and gender, individual patient schedules and summaries, and inventories of forms completed.

